#### The inclusion criteria

The inclusion criteria of participants for investigation and following-up were patients who: (1) had been registered as a managed chronic patient between year 2008 to January 2012, which meant the participants were all aged over 35 and had an official health records including their basic demographic information, symptoms and risk factors, and with a history of hypertension and/or diabetes II no less than six months and taking BP/GLU records at least four times a year; (2) had been consistently enrolled in the new rural cooperative medical scheme; (3) constantly reside in his/her own cluster, which was defined for at least one year before intervention and at least six months after and must ensure that have a complete BP record.

#### The exclusion criteria

The exclusion criteria were those who: (1) had a stable BP/GLU history (consistently under 120/80 mm Hg and 6.5 m mol/L) longer than one year and thus would not admit having chronic diseases or refuse to take medicines; (2) were estimated for a life expectancy less than two years due to old age, venerable situations or severe complications such as cerebral infarction or pancreatic cancer, thus would potentially call for apparent extra samples; (3) would probably get lost in follow-ups with high chances to go out, which was recognised for at least six months away yearly during the intervention period for reasons as migration for work, education or kinship-care-seeking; (4) would hardly visit or investigate due to intellectual or activity incompetence; (5) mentally damaged or communication incapable; (6) refuse to cooperate due to personal reasons. Newly recorded patients between intervention period were not in our sample giving that they would mostly be managed under risk level I and unnecessarily shake the sample structure.

Finally 1641 patients with hypertension and 332 with diabetes II of the total 6833 managed subjects were selected from the record list provided by the local administrator (see Table 4). At the baseline and end-line of this trial, we will take all the samples into statistical examination, checking out if there were any differences.

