## Methodology

### Study design

A clustered randomised controlled trial was used. Nearly 60 clusters/villages in 6 towns and 200 professionals from three levels were intervened, and around 6000 chronic patients were enrolled in this trial. We re-designed the health policy by giving initials to change their delivery and payment system on chronic diseases. There were two basic intervention modes: (1) care integration (MDT and MIP), which was to integrate different caregivers aiming to reshape the solitaire county–town–village service frame into an integrated health care delivery system; (2) payment integration (SGB–P4P), which was to integrate between the delivery system and medical insurance payment system by alternating the original fee-for-service system into a pre-paid system. This strategy aimed to create incentives to help the suppliers to act more willingly or actively. In accordance, the 60 clusters were categorised into three groups: two treatment groups which implemented each of the above strategy; and one control group with no interventions to serve as a natural blank comparison.

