### Sample size and power calculation

Bound by the limited resources, we took several steps to decide the sample size to simplify the management while promise the scientifically meaningful differences. We used Power Analysis and Sample Size (PASS, 11.0) to help us calculate the statistical power and sample size. A statistical power of 80% with 0.05 significance level was chosen.

(1) *Cases of continuity of clinical care*. First, we used *two independent proportion calculation* to estimate the continuous cases needed in terms of *continuity of clinical service* (see “Outcome”), which would mostly constrain the statistical power. The results showed that although 100 cases in the treatment group could promise a required power, with the uncertainty of sample size in control group, we needed at least 120 cases in the treatment group to detect a 20% difference between groups with required significance level (see Table 2). (2) *Sample size*. We decided the minimum sample size based on the knowledge of cases needed and previous data. According to the previous reimbursement records in trial place (2010–2012), the continuous cases accounted for 3.0–5.0% among the chronic hypertensive patients, so with a conservative consideration, we need at least 230–270 individuals per town (530/490 per group) to ensure that we could have 120 continuous cases in each group. (3) *Power calculation*. Third, according to the estimated sample size we re-calculated the statistical powers under other indexes to check out whether that the sample size was sufficient. We chose several main variables and analysis methods to calculate the possible statistical power and output the required odds ratios (see Table 3). (4) *Drop-outs*. Taking a conservative drop-out rate of 20%, we finally arrived at an estimated sample size of 258–324 per town.

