#### Project costing

To make an economic evaluation of the policy trial to compare with the usual care model, we also take records of the extra expenditures of project such as publicity, training, patient ID card production, printing, transportation, meeting organisation, consumables and accommodation. Besides, the increased staff workload is also recorded into counting the cost by adding the working hours into cash under the National Labor Payment Standard and the average local salary. The team coordinators were asked to take a monthly record of all the actual expenditures and increased working hours.

All data were collected through structured patient questionnaire, staff questionnaire, institution investigation, follow-up files, medical records and the reimbursement data that extracted from the local electronic insurance system (see Table 5).

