**Table 2. tb0002:**
[figure not shown]
Minimum cases needed under index “continuity of clinical service”

Summary: group cases of 120/96 or 120/120 in treatment/control group could achieve over 80% power to detect a 0.2000 difference between group proportions.

^a^Considering the intervention effect, we assumed the relation of conforming cases between control/treatment group varied from 0.8–1.0/1.0.

^b^Assumed the detectable proportion of cases conformed to the defined “continuity of clinical service” is 0.5–0.7 in the treatment group and 0.3–0.5 in the control group.

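### The power-limiting continuity outcome, a share read from insurance records, is counted inside the 1,973 sampled patients, who would yield about 16–33 cases per group against the 120 required

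*Protocol article*

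**What the plan says.** All statements are in the Protocol article.

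- **The exclusion criteria** (closing paragraph): "Finally 1641 patients with hypertension and 332 with diabetes II of the total 6833 managed subjects were selected from the record list provided". At baseline and end-line, "we will take all the samples into statistical examination, checking out if there were any differences".
- **Sample size and power calculation**: "A statistical power of 80% with 0.05 significance level was chosen". Continuity of clinical service is named as the index that would limit power most. Step (2) takes from the 2010–2012 reimbursement records that continuous cases make up 3.0–5.0% of hypertensive patients. It then asks for 230–270 people per town (530/490 per group) "to ensure that we could have 120 continuous cases in each group".
- **Table 2, summary line**: "group cases of 120/96 or 120/120 in treatment/control group could achieve over 80% power to detect a 0.2000 difference between group proportions".
- **Project costing** (data sources): the sources include follow-up files, medical records and "the reimbursement data that extracted from the local electronic insurance system".
- **The inclusion criteria**: participants must have been consistently in the insurance scheme. They must have lived in their cluster for a year before the intervention and at least six months after, with a complete BP record.
- **The exclusion criteria**: these include an estimated life expectancy under two years, a predicted long absence during the intervention, and refusal to cooperate.
- **Study design** gives a different count: "around 6000 chronic patients were enrolled in this trial".

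**The concern.** Two kinds of outcome draw on different sources. Drug compliance, SF-36 and lifestyle need an interview, so they need a sample of manageable size. Continuity of clinical service does not: the plan obtained its planning share for this outcome from past insurance records of the trial area. Yet the sizing paragraph requires the interview sample itself to contain the 120 cases per group.

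Two things are at stake. The first is the number of cases for the outcome that the plan treats as its bottleneck. The second is selection. Expected survival, expected absence and willingness to be interviewed can be defended as filters for a questionnaire cohort. They give no reason to drop a patient's insurance claims, and the condition of six months' residence after the intervention lets events after its start decide who is counted. Masking of providers was not feasible.

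**Working it through.** **Inputs.** Sample 1,641 + 332 = 1,973, assuming patients with both diseases are counted once; managed list 6,833; share 3–5%; target 120 cases per group. Table 4 is not shown, so equal thirds are assumed. Where only hypertensive patients count, the list is assumed to have the sample's mix, 1,641/1,973 = 83.2%.

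**1. The plan's own figure.** Two-proportion test, pooled variance, two-sided 0.05, difference 0.20, treatment proportion 0.5–0.7:
- 120/96 gives 83.7–85.3% power.
- 120/120 gives 87.7–89.0% power.

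The claim of over 80% in Table 2 reproduces, without clustering.

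**2. From cases to patients.** 120/0.05 = 2,400 and 120/0.03 = 4,000 patients per group. The stated 490–530 per group would give 490 × 0.03 = 15 to 530 × 0.05 = 27 cases.

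**3. Expected cases per group and power for a 0.20 difference.** Cases = patients per group × 3–5%; same test, equal groups, no clustering.

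| Set | Patients per group | Cases | Power |
|---|---|---|---|
| Sample, hypertensive only | 1,641/3 = 547 | 16–27 | 20–32% |
| Sample, all | 1,973/3 = 658 | 20–33 | 24–38% |
| Managed list, hypertensive only | 6,833 × 0.832/3 = 1,894 | 57–95 | 57–81% |
| Managed list, all | 6,833/3 = 2,278 | 68–114 | 65–87% |

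The period to which the 3–5% refers is not stated. If it is an annual share and cases accrue over 24 months, every count doubles: 33–66 in the sample (36–65% power) and 114–228 on the list (86–99%).

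**4. Share of patients against share of information.** 1 − 1,973/6,833 = 71.1% of listed patients are outside the sample. For an outcome measured on every patient, the variance of a town mean is proportional to (1 − ICC)/m + ICC, with m = 1,973/6 = 329 or 6,833/6 = 1,139. The text gives no ICC, so a range is assumed:

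| Town ICC | Variance, list ÷ sample | Fall |
|---|---|---|
| 0.0005 | 0.39 | 61% |
| 0.001 | 0.46 | 54% |
| 0.005 | 0.73 | 27% |
| 0.01 | 0.84 | 16% |
| 0.02 | 0.91 | 9% |
| 0.05 | 0.96 | 4% |

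Where only cases form the denominator, m is far smaller and the gain larger. With hypertensive patients only, at 3%, there are 16.4/2 = 8.2 against 56.8/2 = 28.4 cases per town. At ICC 0.05 the ratio is (0.95/28.4 + 0.05)/(0.95/8.2 + 0.05) = 0.083/0.166 = 0.50.

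**The case against.** A traced cohort chosen to limit workload is a legitimate design, and which patients serve which outcome is normally settled in the analysis plan. That defence covers silence. It does not cover continuity of clinical service, where the sizing paragraph itself places the cases inside the sample.

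A reader might infer more than the document supports:

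- **That all record-based outcomes are confined to the 1,973.** This is not stated. The eligibility criteria are framed for investigation and follow-up, Study design speaks of about 6,000 enrolled patients, system efficiency is a county-to-township hospital comparison, and Table 5, which would settle it, is not shown. For re-admission and for in-patient use and cost, the point is conditional.
- **That usable records exist for all 6,833.** The text mentions a record list only. Insurance covers over 90% of rural people, not all. Regular and complete BP records are inclusion conditions, so some listed patients may lack them.
- **That BP/GLU readings should also move to the whole list.** The intervention changes monitoring, follow-up and file transfer, so completeness of these readings could differ by arm. Widening the set could then add bias.
- **That the sample is biased between arms.** This is not shown. Patients were drawn by computer-generated random numbers within strata and did not know their group. The 4,860 left out mix random non-selection, which costs precision only, with exclusions, and the split is not given.
- **That 71% of the information is lost.** With two towns per group it is generally less, as step 4 shows.

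It is also fair to say that the main arithmetic fault lies in the conversion from cases to patients. On the 3–5% share taken once, the whole list still falls short of 120.

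**Conclusion.** The point holds for continuity of clinical service and extends to re-admission and in-patient use and cost only if those are also meant to be confined to the sample. The sample is expected to hold about 16–33 continuity cases per group, far below 120; the managed list would hold about 57–114. The counts rest on equal thirds, on listed patients having the same 3–5% share as assumed for the sample, and on claims being available for them; they would fall in proportion to any uninsured share. The power figures ignore clustering and are therefore optimistic.

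This is a worthwhile, inexpensive improvement and not a full rescue. It adds cases where they are scarcest and frees claims outcomes from interview-feasibility filters and from the residence condition after the start of intervention. For outcomes measured on every patient, the gain in precision is small unless the town ICC is well below 0.01.

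**What to change.** State the analysis set for each outcome, and reconcile the roughly 6,000 enrolled with the 1,973 sampled.

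1. **Insurance reimbursement outcomes** (continuity of clinical service; also 30-day re-admission and in-patient use and cost if these were to be restricted to the sample): analyse all patients on the managed list of the six towns, fixed before the intervention, who were in the insurance scheme before it began. Analyse by town of registration, whatever their later residence or contact. Report the 1,973 as a sensitivity analysis.
2. **Questionnaire outcomes and BP/GLU follow-up readings**: keep the 1,973.
3. **Power**: say which period the 3–5% share covers. Restate the expected cases and power for the chosen set, allowing for clustering, because 120 per group is not reached if 3–5% is the share over the whole period.

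The cost is a wider de-identified extraction, the ethics committee's agreement for patients who were not interviewed, and a protocol change. No new patient contact is needed, and the source was already used for 2010–2012. The limits are that questionnaire covariates are missing for the wider set and uninsured patients have no claims.

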### Enrollment and masking

A random sequence of numbers was generated by the computer under each stratify factors. Patient enrollment and investigation were personally done by 12 investigators trained by our research team. All the respondents were irreplaceable samples, meaning that they would be traced through the whole intervention period and accept investigations both in the baseline and end-line study. During intervention, the missing respondents would not be replaced by matching substitution samples, and newly screened out patients during intervention period would not be considered. Due to the trial design of provider intervention, the masking was not feasible, but the patients were not informed with the grouping information and they were not aware of what change would be given to care supply. When trial finished, we will send the database to the third player to do the analysis without giving them the group intervention information.

### Ethical approval

This trial has received ethnical approval from the Tongji Medical College Academic Ethics Committee of Huazhong University of Science and Technology (IORG No: IORG0003571) in June 2012. Patient informed consents were achieved in the baseline investigation.

### Outcomes measures

Basically, we take the period BP/GLU control rate and drug compliance (DC) as the primary outcomes. Period BP/GLU control rate is a new index we create to reflect the consistent BP/GLU control in a certain period, to replace the old index which merely consider if the BP/GLU is safe by the once time assessment. Period BP/GLU control rate takes the fluctuation degree and frequency into account; it changes reversely with the frequency and degree of BP ≥ 140/90 mm Hg (130/80 mm Hg with complications)/GLU ≥ 7.8 m mol/L (after meal) within the total times of BP/GLU assessment. The *BP control rate* is defined as the ratio of systolic pressure under 140 mm Hg (130 mm Hg with complications) among the sample (N), and CT means control times.
[figure not shown]

For the population, we use the arithmetic mean of total individual period BP/GLU control rates to evaluate the group control rate.

*DC rate* is defines as the ratio of good DC among the sample which is measured by the Morisky questionnaire. The BPs are collected at least every three months during the intervention, and the DCs are collected twice at the baseline and end-line investigation.

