#### Multidisciplinary team service

The MDT was developed to help both the primary and hospital care and suppliers integrate under the situation of scarce human resources. Considering the unique county–township–village human resource distribution structure in rural area, we designed a “double L” team – a unique structure to connect three service levels from both horizontal and vertical direction. The upper vertical ladder connected the clinical physicians between county–township level, and the lower vertical ladder connected the primary caregivers between township–village level; and the interphase was the connection of clinical and primary staff through coordination management in township level. In this trial, we enrolled in 15 doctors in each county hospital, 2 from out-patient and 3 from in-patient Departments of Endocrinology, Neurology and Cardiology, to take care of the continuous treatment and contact with the community doctors. In every intervened town we enrolled six staffs: two physicians, one responsible for out-patient and one for in-patient; three primary caregivers, mainly took care of screening, following up and monitoring the chronic patients; and also one team manager/coordinator, to help the team communication and information delivery. In every cluster of the intervened town we enrolled all the village clinicians to help the neighbourhood follow-up. By this means we formed a MDT from different disciplines as primary care, clinical service and management, and also from different organisations as county hospital, township hospital and village clinics; and also made sure there to be at least 17 clinicians, 10 primary caregivers and 4 management staff in every community to serve the chronic patients (see Figure 3).

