#### Multi-institutional clinical and management pathway

Once we built the MDT, we also need a new behaviour mode to instruct the team cooperation. To connect the primary–secondary–tertiary care among community and hospital level, we changed the original segmented practice into a continuous disease-based pathway to integrated care and management comprehensively and jointed efforts from the three levels. The aim was to merge all the services such as screening, diagnosis, treatment, rehabilitation and community management together into a continuous and coordinated care cycle through specific disease pathways and flow management. The pathway composed three parts: (1) the regular community practice provision under stable condition, including screening, BP/risk factor monitoring and follow-up of rehabilitation patients; (2) the continuous clinical treatment under incidence, including medical condition assessment, continuous treatment, variance analysis and rehabilitation; (3) the flow management, including professional contact, referral, file transfer and joint follow-up. Through backstage management tools we connected all the professionals' behaviours into a conjoint medical process by removing what was superfluous and filling in what was missing under the original context.

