#### System global budgets and pay-for-performance (SGB and P4P)

Though MIP and MDT were designed to form a new patient-centred service model, the behind motivation to make it run effectively was still needed. Originally, the suppliers were paid separately from the medical insurance fund without considering if they cooperate, in this case, they would be granted reimbursement whether they performed duplicated exams, prescribed contradictory medicine or had bad control of discharged patients. The whole concept of SGB–P4P system was to better integrate the primary care fund and medical insurance fund together, and to stimulate team staff from different institutions to act for the patient interest. The basic process was: first re-calculating the possible medical consumption per capita in a certain period, and pre-paying the MDT team as a whole without identifying where they came from; second paying based on the cooperation performance; third promising the re-distribution autonomy of the possible savings and paying according to the previous distribution plan. The medical fund officer kept the right to evaluate the team performance, monitor the money re-distribution plan and randomly check to make sure the patients were treated properly. The logic behind the payment system was to encourage the dominant attention on clinical service gradually transfer into the primary care, and avoid inappropriate and unnecessary treatment to the greatest extent by integrating the suppliers into a shared group and force them to think and act for the patient good as much as possible.

To sum up, the MIP was designed to afford a behaviour benchmark, the MDT was designed to distribute role responsibility, and the SGB–P4P was designed to make it effectively and consistently run.

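### The three-monthly readings behind the primary BP/GLU control rate are apparently recorded by the unmasked care teams under test, and no check on recording limits what is claimed for the payment system

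*Protocol article*

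**What the plan says.** Under Outcomes measures, "we take the period BP/GLU control rate and drug compliance (DC) as the primary outcomes". The period rate depends on how often and how far readings exceed the cut-off, "within the total times of BP/GLU assessment". The same section also gives a simpler ratio of systolic readings below 140 mm Hg (130 with complications). The formula itself is a figure that is not shown. On timing: "The BPs are collected at least every three months during the intervention, and the DCs are collected twice at the baseline and end-line investigation".

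Four other sections bear on who takes these readings:

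- **Enrollment and masking.** Twelve trained investigators enrol and investigate patients, who "accept investigations both in the baseline and end-line study". On providers: "Due to the trial design of provider intervention, the masking was not feasible". Patients are not told their group, and the analyst is not given the group intervention information.
- **Multidisciplinary team service.** Each intervened town has "three primary caregivers, mainly took care of screening, following up and monitoring the chronic patients", and village clinicians help with follow-up.
- **Multi-institutional clinical and management pathway.** Regular community practice is described as "including screening, BP/risk factor monitoring and follow-up of rehabilitation patients".
- **Project costing.** The data sources listed include follow-up files and medical records.

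Under System global budgets and pay-for-performance, the team is prepaid as a whole, followed by "second paying based on the cooperation performance; third promising the re-distribution autonomy of the possible savings". The fund officer's random check concerns whether patients are treated properly. Under Hypothesis, Assumption 2 (the payment effect) is tested by comparing the two treatment groups.

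**The concern.** If the caregivers record the readings, the people whose behaviour the trial sets out to change also produce a primary outcome, and they know which scheme they work under. The index depends on a cut-off, so small differences in rounding, in repeating a high reading or in choosing which reading to file can move it without any change in true BP.

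Assumption 2 is the most exposed comparison. The financial arrangement is what is meant to separate the two treatment groups, so any recording habit that follows the arrangement would appear as a payment effect. A recording difference between the intervened towns and the control towns would affect Assumption 1 in the same way.

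**Working it through.** **Step 1: who records the readings.** No single sentence says. The passages side by side:

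| Point | Section | What it implies |
|---|---|---|
| BP at least every three months; drug compliance only at baseline and end-line | Outcomes measures | The BP series runs on a schedule of its own, outside the two investigations |
| Investigators do enrolment, baseline and end-line | Enrollment and masking | No interim readings are assigned to them |
| Caregivers follow up and monitor; BP monitoring is part of the pathway | Multidisciplinary team service; Multi-institutional pathway | Interim BP belongs to the team's routine work |
| Eligible patients already have at least four BP/GLU records a year | The inclusion criteria | The routine record has the same frequency as the outcome |
| Sources include follow-up files and medical records | Project costing | Of the sources listed, only these could plausibly hold a three-monthly series |

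Together these support the reading that the caregivers apparently record the series. The schedule sentence names BP only. That glucose comes from the same files is an assumption.

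**Step 2: do the safeguards reach the recording?** Write the recorded rate in group g at time t as true rate + e(g,t), where e is recording error. Difference-in-differences then estimates

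true effect + [e(1,post) − e(1,pre)] − [e(0,post) − e(0,pre)].

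The error terms cancel if e is constant over time within each group, or changes equally in both. They do not cancel if e changes with the intervention in one group. Masking the analyst acts after the values are written. The fund officer's check concerns treatment, not readings.

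**Step 3: size, as an illustration only.** The plan states no figure on this point to reproduce. It gives no BP mean or SD, so these are assumed: systolic readings normal with mean μ = 135 to 150 and SD σ = 14 to 18 mm Hg.

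P(140 ≤ SBP < 145) = Φ((145 − μ)/σ) − Φ((140 − μ)/σ)

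| σ | μ = 135 | μ = 140 | μ = 145 | μ = 150 |
|---|---|---|---|---|
| 14 | 0.123 | 0.140 | 0.140 | 0.123 |
| 18 | 0.101 | 0.109 | 0.109 | 0.101 |

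If a share s of these readings is written as below 140 in one group only, the simple below-140 rate rises by s × P:

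- s = 0.25: 0.25 × 0.101 to 0.25 × 0.140 = 2.5 to 3.5 points
- s = 0.50: 5 to 7 points
- s = 0.75: 7.6 to 10.5 points

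**Step 4: could a shift of this order matter?** Suppose 10% of all high readings are recorded as controlled in one group. The recorded rate becomes p + 0.10(1 − p). Take 1641/3 = 547 hypertensive patients per group (an even split is assumed), one binary reading each, two-sided 0.05 and no true effect:

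| True rate p (assumed) | Recorded rate | Chance of p < 0.05, no clustering | Design effect 2 (assumed) | Design effect 5 (assumed) |
|---|---|---|---|---|
| 0.15 | 0.235 | 0.95 | 0.71 | 0.36 |
| 0.30 | 0.37 | 0.69 | 0.41 | 0.19 |
| 0.50 | 0.55 | 0.38 | 0.22 | 0.11 |

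Modest recording differences could therefore produce an apparent effect. How readily depends heavily on the assumed rate and on the clustering.

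**The case against.** A good deal can be said on the other side.

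- **The recorder is inferred.** Table 5, which covers data collection, is not shown and could name another source. The article also says patients are traced throughout, without saying by whom. This stands, and it is why the point says apparently.
- **Pay is not tied to BP.** A reader might infer that staff are paid for controlled BP. The documents do not support that. The stated criterion is cooperation performance, and writing a lower value does not itself create savings. What remains is an indirect incentive that differs by group, added to the lack of masking.
- **The index is more than a count below a cut-off.** It also takes degree into account. If degree is weighted, moving values from 140–144 to just below 140 could change it by less than Step 3 shows.
- **The inputs are assumed.** The assumed means put 24–64% of readings below 140. The Trial setting section reports under 15% with both good control and good compliance, which is not directly comparable. If only 15% were below 140, the 140–144 band would hold about 7–10%.
- **There are cross-checks.** A reader might infer that a positive payment result could never be told apart from better-looking records. That goes too far. Drug compliance, the other primary outcome, is measured at the two investigations, and reimbursement data are also collected. These are only partial checks, because none of them verifies BP itself.
- **Routine data are a common pragmatic choice in system-level trials, and the article admits that masking was not feasible.** True, but the admission does not bound the effect on this outcome.

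**Conclusion.** The point holds as a risk of detection bias in a primary outcome, most relevant to Assumption 2. It rests on an inference from several sections about who records the readings, and on the possibility that recording changes with the intervention in one group. The documents contain no evidence that readings are misrecorded, and the point should not be read as saying so.

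Under the stated assumptions, a simple below-140 rate could move by about 2.5–10.5 points with no true change. The period index could move less. The figures show scale and do not predict bias.

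A reader might also conclude that the period rate should give way to an investigator's reading as the confirmatory measure. The documents do not support that. The index was built to replace one-time assessment, the investigators are not stated to be masked, and it is not stated that they measured BP at baseline. Severity is below must-fix: the analysis needs a check and a limit on the claim, not a new primary outcome.

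**What to change.** 1. Keep the period control rate as primary. State who takes and files the three-monthly readings and, if it is so, that they are provider-recorded and unmasked.
2. Pre-specify a recording check from the existing files, by group and over time, covering end-digit distribution, heaping just below the cut-off and number of readings per patient. The heaping comparison needs care, because a true fall in BP also shifts readings across the cut-off.
3. Add a sensitivity analysis on BP/GLU taken by the trained investigators at end-line, with their baseline value where one was recorded. Report its agreement with each patient's last file reading.
4. Report a payment effect on BP/GLU control as supported only if this analysis agrees in direction. Otherwise state that recording differences cannot be excluded.

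**Cost.** Some extra analysis of data already held, and one reading at the end-line visit planned for May 2015 if it is not taken now. The sensitivity analysis rests on a single, noisier reading. If the investigators took no BP/GLU at the July–August 2012 baseline, that value cannot be recovered and the analysis compares end-line values only.
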